** *MRI* **													
*Structural*		x					x					x	
*Functional*		x					x					x	
													
** *Behavioural* **													
*Oura Ring (Ongoing)*	x	x	x	x	x	x	x	x	x	x	x	x	
*Heart Rate Discrimination Task*						x					x		
													
** *Qualitative* **													
*Unstructured Interview*	x												
*Semi-structured interview*		x				x					x	x	x

**Table 5 T5:** Summary of timepoints for analysis.

PsiloPain Outcome Measures	
*Measure*	Timepoints for Analysis
Primary Outcome Measures	
Neurophysiology	
*Lempel-Ziv complexity (LZc) (EEG)*	DD1 vs DD2
*Modularity (MRI)*	Prep 1 vs Prep 2 vs FFU
Secondary Outcomes	
Neurophysiology	
*Plasticity via vLTP paradigm (EEG)*	FU1 vs FU2
*Predictive Processing via rMMN (EEG)*	FU1 vs FU2
*Alpha power (EEG)*	DD1 vs DD2
*DTI (MRI)*	Prep 1 vs Prep 2 vs FFU
Physiology	
*Heart rate Variability (Oura)*	4 weeks Post-Dose 1 vs 4 weeks Post-Dose 2
*Sleep Quality (Oura)*	4 weeks Post-Dose 1 vs 4 weeks Post-Dose 2
*Interoception (Heartrate Discrimination Task)*	FU1 vs FU2
Primary Patient Reported Outcome Measures	
*Brief Experiential Avoidance Questionnaire (BEAQ)*	Baseline to primary endpoint
Secondary Patient Reported Outcome Measures	
*Core Pain Outcomes*	FU1 vs FU2
*Acute Mediators*	DD1 vs DD2
*Wellbeing/Mental Health Outcomes*	FU1 vs FU2
*Qualitative*	
*Interviews*	Prep 1 vs FFU

#### Mechanistic neurophysiology measures

The present study is conceived as an early-phase mechanistic study, intended to investigate the central action of psychedelics in a population of people living with fibromyalgia. EEG will be recorded at 6 visits: screening, Dose 1, Integration 1, Dose 2, Integration 2, and Final Follow Up (see **Table 3**).

The primary outcome measure is Lempel-Ziv Complexity (LZc) of the resting state EEG signal during dosing days as detailed above. LZc is a compressibility algorithm used to measure signal diversity and has been previously investigated in psychedelic contexts (91–93). Here we hypothesise an increase in LZc under psilocybin.

In addition to resting state, participants will complete the visual Long-Term Potentiation (vLTP) (94) and roving Mismatch Negativity (rMMN) (95, 96) tasks at integrations to investigate the post-acute neuroplasticity and predictive coding. We also hypothesise reduced alpha power under psilocybin.

We will complement these measures with structural and functional MRI data. We will collect MRI data at 3 timepoints: Prep 1, Prep 2, and Final Follow Up (see **Table 3**). We will investigate changes in resting-state activity and connectivity, as well as structural changes including diffusion imaging. We hypothesise decreases in brain network modularity after PAT and decreases in diffusivity in prefrontal to subcortical region white-matter tracts, indexed by the diffusion imaging.

#### Patient reported outcome measures

While the primary interest of the study is in the neural mechanisms involved in psychedelic-mediated action in a fibromyalgia population, we will also collect efficacy measures at every timepoint of the study. Patient-reported outcome measures (PROMs) will be collected in-person and remotely (via video calls and the online survey platform “Alchemer”). All baseline measurements will be taken at Prep 1, except for Symptom Severity Score and the Widespread Pain Index which will be collected at the Screening Visit. Baseline EEG and MRI will be collected at screening and Prep 1 visits, respectively. All primary endpoint measurements (including EEG and MRI) will be collected at final follow up (8 weeks after prep 1). Please see **Tables 2**, **3** for a full list of PROMs.

PROMs are grouped as “Core Pain Outcomes,” “Wellbeing/Mental Health Outcomes,” or “Acute mediators” (see table). We will also be collecting “Patient Impression Measures” to assess the effects of expectancy and blinding efficacy. We will assess the therapeutic relationship using the STAR outcome measure, filled in by both patients and their guides. We hypothesise improvements in Core Pain Outcomes and Wellbeing/Mental Health Outcomes.

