** *Sub-Acute Change Measures* **														
*Brief Pain Inventory Short Form*	x	x	x	x		x	x			x	x	x	x	x
*Single Item Sleep Score*			x	x		x	x	x		x	x			
*9-Item Patient Health Questionnaire (PHQ-9)*		x									x	x	x	x
*Warwick-Edinburgh Mental Wellbeing Scale (WEMWBS)*		x									x	x	x	x
*7-Item Generalised Anxiety Disorder Questionnaire (GAD-7)*		x									x	x	x	x
*Brief Experiential Avoidance Questionnaire (BEAQ) *		x									x	x	x	x
*Snaith-Hamilton Pleasure Scale (SHAPS)*		x				x				x	x			
*Chronic Pain Self-Efficacy Scale (CPSS)*		x									x			x
*Watts Connectedness Scale (WCS) *		x									x			
*Function of Self-Criticizing/Attacking Scale (FSCS)*		x									x			
*The Self Experiences Questionnaire (SEQ)*		x									x			
*8-item Committed Action Questionnaire (CAQ-8)*		x									x			x
*8-item Chronic Pain Acceptance Questionnaire (CPAQ-8)*		x									x			x
*Fibromyalgia Impact Questionnaire (FIQ)*		x									x			x
*Multidimensional Assessment of Interoceptive Awareness (MAIA)*		x									x			x
*Pain Catastrophizing Scale (PCS) *		x				x				x	x			x
*Experiences in Close Relationships Questionnaire (ECR-M16)*		x									x			
*Psychological Inflexibility in Pain Scale (PIPS)*		x									x			x
*Cognitive Fusion Questionnaire (CFQ)*		x									x			x
*Metaphysical Beliefs Scale (Self-Constructed)*		x									x			x
*Somatic Processing Questionnaire (Self-Constructed)*						x				x				
*The Centrality of Events Scale (Short Version)*						x				x	x			x
*Multifaceted Psychological Integration Assessment (M-PIA)*		** **				x				x	x	x		x

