### Analysis strategy

Our two primary, mechanistic hypotheses relate to EEG and MRI:

H1 (EEG): We hypothesise an increase in signal complexity (LZc) at peak drug effects under psilocybin.H2 (fMRI): we hypothesise a decrease in brain network modularity after PAT.

Secondary outcomes include:

Reduced alpha power under psilocybin.A relationship between acute increases in LZc and post-PAT changes in psychological flexibility, measured by the BEAQ.Changes in mass univariate functional connectivity after PAT.Changes in PFC-tract diffusivity after PAT.Changes in EEG ERP related markers of functional plasticity after PAT.Changes in pain symptomatology after PAT, measured by the BPI-IS.

All secondary outcomes will be exploratory (see **Table 5**). Sub-acute EEG analyses will follow previously outlined protocols (91–93). With an assumption of high co-linearity between core outcomes we would explore data reduction approaches (e.g., factor or principal component analyses or canonical correlation analysis) to investigate key contrasts. Two tailed tests will be performed if findings are not aligned with prior hypotheses. Due to prior hypotheses (above) on directionality, one tailed t-tests will be appropriate to perform for H1 & H2. Multiple comparisons corrections and Bayesian analyses will be performed where deemed appropriate. Please see **Table 5** for timepoints for each analysis.

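### Table 5 analyses the pain and mental-health questionnaires as FU1 vs FU2, where PHQ-9, GAD-7 and WEMWBS are not collected and where pain change from before therapy is not measured

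*Protocol article*

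**What the plan says.** Under Patient reported outcome measures, the Protocol article groups the questionnaires and gives the hypothesis: "We hypothesise improvements in Core Pain Outcomes and Wellbeing/Mental Health Outcomes". Under Analysis strategy, the pain aim is listed as "Changes in pain symptomatology after PAT, measured by the BPI-IS". That section sends the reader to Table 5 for the timepoints of each analysis.

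Table 5 gives Core Pain Outcomes and "Wellbeing/Mental Health Outcomes" the contrast FU1 vs FU2. BEAQ, the primary patient-reported outcome, is instead analysed as "Baseline to primary endpoint". The article does not define FU1 or FU2, and it does not list which scales belong to which group.

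On baseline timing, Patient reported outcome measures says: "All baseline measurements will be taken at Prep 1, except for Symptom Severity Score and the Widespread Pain Index". The same section places primary endpoint measurements at final follow-up, 8 weeks after Prep 1.

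**The concern.** The hypotheses are about improvement and about change after therapy. The contrast in Table 5 uses two visits that both follow a dosing session. Two problems result. Some scales that plainly concern mental health and wellbeing have no data at those visits. For the scales that do have data, the contrast answers a different question: whether the state after session 2 differs from the state after session 1.

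The article says the study should inform a possible later RCT. A null FU1 vs FU2 result could be read there as no benefit when it shows only no difference between sessions. Where no data exist, the analysts would have to choose other timepoints later, which would depart from the published plan.

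**Working it through.** **Step 1. What FU1 and FU2 are.** Study visits counts three follow-up sessions among the eight visits. By the tables, these are Integration 1 (visit 4, Day 2), Integration 2 (visit 7, Day 31) and Final Follow Up (visit 8, Day 59). Table 5 uses a separate label, FFU, for the last. It also gives FU1 vs FU2 to vLTP, rMMN and the heart-rate discrimination task, which Table 4 collects only at Integrations 1 and 2. So FU1 is Integration 1 and FU2 is Integration 2. Each falls one day after dosing (Days 1 and 30).

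**Step 2. Which scales have data there.** Reading the 23 sub-acute rows of Table 3 by column:

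| Marked at Integrations 1 and 2 | Rows | Scales |
|---|---|---|
| Both | 7 | BPI, sleep item, SHAPS, PCS, Somatic Processing, Centrality of Events, M-PIA |
| Neither | 16 | PHQ-9, WEMWBS, GAD-7, BEAQ, CPSS, WCS, FSCS, SEQ, CAQ-8, CPAQ-8, FIQ, MAIA, ECR-M16, PIPS, CFQ, Metaphysical Beliefs |

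PHQ-9, GAD-7 and WEMWBS are marked at Remote Baseline, Final Follow Up and the extended follow-ups only. BEAQ has exactly the same schedule, and Table 5 gives it a contrast that this schedule supports.

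**Step 3. What the contrast estimates when data exist.** Let d1 and d2 be the mean improvements from baseline at FU1 and FU2. Then

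FU1 vs FU2 = d2 − d1, whereas baseline vs FU2 = d2.

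The article gives no effect size, SD or power for these outcomes, so there is no figure to reproduce. As an illustration, assume n = 20, an SD of paired differences of 1 for both contrasts, a one-sided 5% level and a normal approximation:

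power = Φ(δ√20 − 1.645), with √20 = 4.472.

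| d1 | d2 | FU1 vs FU2: δ | Power | Baseline vs FU2: δ | Power |
|---|---|---|---|---|---|
| 1 | 1 | 0 | Φ(−1.645) = 5% | 1 | Φ(2.827) = 99.8% |
| 1 | 1.2 | 0.2 | Φ(−0.751) = 22.6% | 1.2 | about 100% |
| 0.5 | 1 | 0.5 | Φ(0.591) = 72.3% | 1 | 99.8% |
| 0 | 1 | 1 | 99.8% | 1 | 99.8% |

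The 5% in the first row is the false-positive rate. Only in the last row, with no change after session 1, do the two contrasts agree.

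**Step 4. The baseline.** Table 3 marks 19 of the 23 rows at Remote Baseline (Day -7). Of these, only BPI is also marked at Prep 1, so 18 rows, BEAQ among them, are collected at Remote Baseline and not at Prep 1. The sleep item is marked at Prep 1 and not at Remote Baseline. The other three (Somatic Processing, Centrality of Events, M-PIA) have no pre-dose value: 19 + 1 + 3 = 23. The statement that baseline is taken at Prep 1 therefore contradicts the schedule for most of the questionnaires.

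**Step 5. Whether a matching contrast is available.** The 19 Remote Baseline rows and the sleep item are all marked at Final Follow Up. So 20 of 23 rows support baseline vs final follow-up without new data.

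**The case against.** The strongest reply concerns the design. Session content is deliberately withheld, participants receive psilocybin at least once in a single-blind fixed sequence, and the EEG complexity outcome is itself contrasted between the two dosing days. If the sessions differ by design, FU1 vs FU2 is the natural post-acute counterpart. A reader might infer that this contrast can never show improvement, and the documents do not support that: if nothing changes after session 1, it carries the whole improvement (last row of the illustration). What remains is that this depends on an undisclosed condition, and that the difference would still be confounded with time and order in a single arm.

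A reader might also infer that no mental-health scale is collected at the integrations. That is too broad. SHAPS is collected at both, and group membership is not listed. For the same reason, 16 of 23 describes the schedule and does not count affected outcomes: it includes BEAQ, which has its own contrast, and scales that may belong to neither group.

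Two general sentences suggest wider collection than Table 3: efficacy measures at every timepoint (Patient reported outcome measures), and questionnaires collected remotely after each visit (Psychedelic assisted therapy). They name no scale, and the article refers to Tables 2 and 3 for the full list. If they did override Table 3, PHQ-9, GAD-7 and WEMWBS could be contrasted, but still between two post-session days.

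Finally, all secondary outcomes are declared exploratory, and both baseline timepoints precede any dosing. Both points stand and limit the seriousness.

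**Conclusion.** The point holds. The FU1 vs FU2 analysis cannot be done for PHQ-9, GAD-7 and WEMWBS on the Table 3 schedule. For BPI, PCS and SHAPS it can be done, but it measures a between-session difference and not the hypothesised change from before therapy. That difference can be zero despite a large benefit. The Prep 1 baseline statement contradicts Table 3 for 18 of 23 rows, including BEAQ.

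The conclusion rests on reading FU1 and FU2 as the two integrations, which the vLTP, rMMN and heart-rate discrimination rows support, and on taking Table 3 as the operative schedule. The power figures are illustrations under an assumed SD and assumed improvements.

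A reader might infer that the trial's main hypotheses are untestable or that it would end by reporting no benefit. Neither follows. H1 and H2 are not affected, BEAQ already has a suitable contrast, and the data for a matching analysis of the clinical scales are already scheduled. This is a should-fix inconsistency in exploratory secondary outcomes.

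**What to change.** 1. In Table 5, set the contrast for Core Pain and Wellbeing/Mental Health outcomes to baseline vs final follow-up, as already done for BEAQ. Take baseline from Remote Baseline where Table 3 collects it, and from Prep 1 for the sleep item.
2. Keep FU1 vs FU2 only as a labelled between-session comparison, for scales collected at both integrations, and state that it is confounded with time and order. Use change from a pre-session value only for BPI, which has Prep 1 and Prep 2 values. PCS and SHAPS have no value shortly before session 2, so change scores of that kind are not available for them.
3. Define FU1 and FU2, and list the scales in each outcome group. Any listed scale without a pre-dose value (Somatic Processing, Centrality of Events, M-PIA) can have only post-session comparisons.
4. Correct the baseline sentence under Patient reported outcome measures to match Table 3, and reconcile the two general sentences on collection at every timepoint or visit.

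The cost is wording in one table and two sections. No new assessment is needed.

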#### Behavioural and physiological

We will collect 2 other types of behavioural data investigating interoception and physiology (see **Table 4**). Changes in interoceptive accuracy will be measured using the Heartrate Discrimination Task (HRD) (97) at Integrations 1 and 2.

Physiological data including heart rate variability (HRV), actigraphy, and sleep staging will be collected using a wearable device throughout the study.

#### Qualitative

Qualitative data will be collected in the form of semi-structured interviews at Prep 1, Integrations 1 and 2, Final Follow Up, and the 6-month Remote follow up (see **Table 4**). The aims of these interviews are to assess how they lived experience of fibromyalgia change after psychedelic-assisted therapy, as well as its potential therapeutic mechanisms. Patient reports often capture subtle yet powerful changes in personal narratives before and after psychedelic therapy that quantitative data are not able to record.

### Analysis strategy

Our two primary, mechanistic hypotheses relate to EEG and MRI:

H1 (EEG): We hypothesise an increase in signal complexity (LZc) at peak drug effects under psilocybin.H2 (fMRI): we hypothesise a decrease in brain network modularity after PAT.

Secondary outcomes include:

Reduced alpha power under psilocybin.A relationship between acute increases in LZc and post-PAT changes in psychological flexibility, measured by the BEAQ.Changes in mass univariate functional connectivity after PAT.Changes in PFC-tract diffusivity after PAT.Changes in EEG ERP related markers of functional plasticity after PAT.Changes in pain symptomatology after PAT, measured by the BPI-IS.

All secondary outcomes will be exploratory (see **Table 5**). Sub-acute EEG analyses will follow previously outlined protocols (91–93). With an assumption of high co-linearity between core outcomes we would explore data reduction approaches (e.g., factor or principal component analyses or canonical correlation analysis) to investigate key contrasts. Two tailed tests will be performed if findings are not aligned with prior hypotheses. Due to prior hypotheses (above) on directionality, one tailed t-tests will be appropriate to perform for H1 & H2. Multiple comparisons corrections and Bayesian analyses will be performed where deemed appropriate. Please see **Table 5** for timepoints for each analysis.

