**Methods:**

Twenty participants with fibromyalgia will complete 8 study visits over 8 weeks. This will include two dosing sessions where participants will receive psilocybin at least once, with doses varying up to 25mg. Our primary outcomes are 1) Lempel-Ziv complexity (LZc) recorded acutely using EEG, and the 2) the (Brief Experiential Avoidance Questionnaire (BEAQ) measured at baseline and primary endpoint. Secondary outcomes will aim to capture broad aspects of the pain experience and related features through neuroimaging, self-report measures, behavioural paradigms, and qualitative interviews. Pain Symptomatology will be measured using the Brief Pain Inventory Interference Subscale (BPI-IS), physical and mental health-related function will be measured using the 36-Item Short Form Health Survey (SF-36). Further neurobiological investigations will include functional MRI (fMRI) and diffusion tensor imaging (changes from baseline to primary endpoint), and acute changes in pre- vs post-acute spontaneous brain activity – plus event-related potential functional plasticity markers, captured via EEG.

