## Overview/aims

This paper presents the protocol for a mechanistic study investigating the effects of PAT in a fibromyalgia population. The principal focus of this trial is the central mechanism(s) of psilocybin i.e., in the brain and on associated mental schemata, primarily captured by electroencephalography (EEG) recordings of the acute psychedelic state. Secondary outcomes will aim to capture broad aspects of the pain experience and related features through Magnetic Resonance Imaging (MRI), self-report measures, behavioural paradigms, and qualitative interviews. This study aims to serve as a preliminary investigation into potential mechanisms of psilocybin in this study population. By publishing our protocol before commencing data collection, we aim to contribute towards a scientific culture of openness and rigor.

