## Methods and analysis

Here we describe a single arm, fixed sequence, single-blind, within-subjects study. Our primary outcomes investigate psychological flexibility through potential neurophysiological markers (specifically Lempel-Ziv complexity (LZc) recorded acutely using EEG, and the (Brief Experiential Avoidance Questionnaire (BEAQ) measured at baseline and primary endpoint). Secondary outcomes will provide a context to complement these mechanistic EEG data. Pain symptomatology will be measured using the Brief Pain Inventory Interference Subscale (BPI-IS) and broader aspects of health, including physical and mental health functioning will be measured using the 36-Item Short Form Health Survey (SF-36). We will additionally collect self-reported data on the strength of personally held negative beliefs in line with the relaxed beliefs under psychedelics model (55).

Further neurophysiological investigations will include functional magnetic resonance imaging (fMRI and DTI) (changes from baseline to primary endpoint), and EEG (changes from baseline to in putative resting state and ERP plasticity markers. We believe that a breakthrough on the brain mechanisms involved in therapeutically relevant change process catalysed by psilocybin, will have broad and important scientific and clinical implications.

Patient and public involvement (PPI) was used throughout the process of trial preparation and contributed to protocol development. PPI is an emerging research method across mental health and within psychedelic research (76, 77). The method aims to produce research “with” rather than “for” people with lived experience. Such co-created research fosters empowerment and trust in research produces relevant and transparent outputs (78).

PPI informed our therapeutic protocols, inspired further research questions, and resulted in the development of novel measures investigating the somatic elements of the psychedelic experience [see Bornemann et al. (79)]. Further, our panel of patient contributors has provided input to, and approved all patient facing documents.

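### The article gives incompatible sets of primary outcomes: LZc with BEAQ, LZc with fMRI modularity, or all three

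*Protocol article*

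**What the plan says.** The article designates primary outcomes in several places.

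- **Abstract, Methods:** "Our primary outcomes are 1) Lempel-Ziv complexity (LZc) recorded acutely using EEG, and the 2) the (Brief Experiential Avoidance Questionnaire (BEAQ". This is a numbered list of two, without an MRI outcome. Neuroimaging comes under the secondary outcomes.
- **Overview/aims:** "Secondary outcomes will aim to capture broad aspects of the pain experience and related features through Magnetic Resonance Imaging (MRI". EEG is the principal focus.
- **Methods and analysis, opening:** "Our primary outcomes investigate psychological flexibility through potential neurophysiological markers (specifically Lempel-Ziv complexity (LZc) recorded acutely using EEG", and the same sentence adds the BEAQ. Functional MRI and diffusion imaging follow as further investigations.
- **Table 5:** LZc and modularity stand under the primary outcome measures. The BEAQ (baseline to primary endpoint) stands under a separate heading, "Primary Patient Reported Outcome Measures".
- **Mechanistic neurophysiology measures:** "The primary outcome measure is Lempel-Ziv Complexity (LZc) of the resting state EEG signal during dosing days", in the singular. Modularity is hypothesised in the same subsection, as part of MRI data that complement the EEG, and is not called primary.
- **Analysis strategy:** "Our two primary, mechanistic hypotheses relate to EEG and MRI". H1 is LZc. For H2, "we hypothesise a decrease in brain network modularity after PAT". BEAQ appears only in a secondary item, its relationship with the acute LZc increase, and "All secondary outcomes will be exploratory". One-tailed t-tests are allowed for H1 and H2. Multiplicity correction is left to judgement.

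**The concern.** The Abstract and the Analysis strategy each count two primaries and disagree on the second. A later report could headline LZc with BEAQ, or LZc with modularity, and cite this article as pre-specification for either. The second primary could then be picked by its result.

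The section that sets out the analysis also gives no hypothesis or sidedness for BEAQ change, although three other places make it primary. The article says that it is published before data collection for the sake of openness and rigour, and that its results should inform a later randomised trial. An unsettled primary set works against both aims. A separate analysis plan could add detail, but it could not agree with all of these lists at once.

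**Working it through.** The article gives no alpha, power or effect size, so there is no figure of its own to reproduce. The main check is textual.

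| Place | LZc | BEAQ change | Modularity |
|---|---|---|---|
| Abstract | primary | primary | not listed; neuroimaging secondary |
| Overview/aims | EEG is the focus | not named | not named; MRI secondary |
| Methods and analysis, opening | primary | primary | not listed; fMRI further |
| Table 5 | primary | primary (patient-reported) | primary |
| Mechanistic neurophysiology measures | primary, singular | not mentioned | hypothesised, not called primary |
| Analysis strategy | primary (H1) | no hypothesis | primary (H2) |

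This gives three incompatible sets: {LZc, BEAQ}, {LZc, modularity} and {LZc, BEAQ, modularity}. LZc is in each of them.

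**Illustration of the error rate.** Assumptions: the same alpha for each test (0.05, with 0.025 as the lower end of the range), no correction, all null hypotheses true, independent tests. The chance of at least one false positive among k tests is 1 − (1 − alpha)^k.

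- One primary: 5.0% at 0.05; 2.5% at 0.025.
- Two primaries: 1 − 0.95² = 9.75%; 1 − 0.975² = 4.9%.
- Three primaries: 1 − 0.95³ = 14.3%; 1 − 0.975³ = 7.3%.

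Correlation between the tests lowers these figures. With jointly normal statistics, all tests one-sided at 0.05, two and three primaries give 8.8% and 11.8% at a pairwise correlation of 0.5, and 8.0% and 10.3% at 0.7.

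**Price of control.** For an overall 0.05, the first Holm step is 0.05/3 = 0.0167 with three primaries. Take a paired t-test with n = 20 (the article's maximum) and 80% power, from the noncentral t distribution. The standardised paired difference that can be detected is about 0.66 at two-sided 0.05 and about 0.78 at two-sided 0.0167.

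**The case against.** The strongest defence is that Table 5 reconciles the text. It separates primary neurophysiology from a primary patient-reported outcome, and the Analysis strategy limits its pair to mechanistic hypotheses, so H1 and H2 need not demote BEAQ. Listing MRI as a class among the secondaries is also not decisive, since the Abstract lists self-report measures there too while making BEAQ primary. This has force, but it does not explain why the Abstract's numbered list and the opening of Methods and analysis leave modularity out. It also leaves BEAQ change without a primary hypothesis.

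Some stronger readings are tempting but are not supported.

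- A reader might infer that BEAQ is both primary and exploratory. The exploratory item is the association between LZc and BEAQ change. BEAQ change itself is nowhere called exploratory.
- A reader might infer that any two of the three outcomes could be claimed as the primaries. No place supports BEAQ with modularity without LZc.
- The singular wording on LZc could be taken as a further set that excludes BEAQ. It stands in a neurophysiology subsection, where a questionnaire would not be expected. It conflicts only with modularity being primary.
- A higher error rate could be obtained by adding the rule that switches to two-tailed tests when results go against the hypothesis. That rule is a separate defect, and one-tailed testing is stated for H1 and H2 only, so it should not be carried over to BEAQ.

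It is also fair to say that the correction method and alpha may sit in an analysis plan not shown, and that this is a single-arm, early-phase mechanistic study. Their absence alone is no finding. The harm is selective emphasis, not a failed success criterion.

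**Conclusion.** The point holds as a contradiction in the printed text: three incompatible primary sets, with only LZc common to them, and one named primary (BEAQ change) with no hypothesis or sidedness in the Analysis strategy. It needs correcting because the primary outcomes cannot be determined from the article.

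That conclusion rests on the text and not on the error rates. The 9.75% and 14.3% (4.9% and 7.3% at the lower level) show scale only. They depend on an assumed alpha, on independence and on no correction being applied, whereas the article does foresee correction at discretion. The documents do not support a claim that the error rate is known to be inflated by a given amount.

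**What to change.** State one primary list, in the same words, in the Abstract, Overview/aims, Methods and analysis, Table 5, Mechanistic neurophysiology measures and Analysis strategy. Add to the Analysis strategy a stated test and sidedness for BEAQ change from baseline to the primary endpoint. Then choose one of two structures:

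1. LZc as the single primary, with BEAQ change and modularity as named key secondaries tested by Holm. LZc needs no split of alpha. Say whether the two are tested only if LZc is positive. Without that condition, Holm protects the pair and not all three together.
2. All three as primaries, with Holm across them.

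The choice is a scientific one for the sponsor and should be made, and dated, before data are seen. The registration cited in the article was not available for this review and should be checked against the settled list.

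The cost is wording. The second structure also costs sensitivity: at n = 20, the first Holm step needs a standardised difference of about 0.78 for 80% power, against about 0.66 for a single two-sided 0.05 test. The first structure avoids that cost for LZc but gives up primary status for BEAQ and modularity.
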